**Figure 3 figure3:**

SMI Eye Tracking Glasses with 3D reflective markers.

#### Qualisys System

Qualisys is a motion capture system used to track movement. Small retro-reflective markers reflecting infrared light are attached to the participant’s skin. Frame-by-frame analysis is used to track each marker from one frame to the next. Each marker data and their 3D position trajectory can be used to calculate joint and movement trajectories. The force plates and SMI eye tracker are integrated and time synced in the Qualisys system. The SMI program is installed on the Qualisys system. The data from the SMI system are synchronized to Qualisys via a start command, so as to capture its data together with all the other data in the Qualisys system. The force plates are connected to the Qualisys computer via an analog board to capture analog signals from the force plate with the motion capture data. The data from the force plates are synchronized with the motion capture data via a synchronization signal between the Qualisys camera system and the analog board. The sync signal from the camera system is connected to an external trigger input on the analog board to start the capture of analog data using hardware synchronization.

Kinematics will be measured using an infrared motion analysis capture system, consisting of 9 Oqus 3D Motion analysis capture units. A set of 27 reflective markers will be placed on the participant. Markers will be attached using a double-sided tape directly onto the skin. Pelvis markers will be placed in accordance with the modified Helen Hayes model as a set of 3: 1 marker on each anterior superior iliac spine and 1 on sacrum (midpoint). For the thigh segment, markers will be placed on midthigh, medial femur epicondyle, and femur lateral epicondyle for each extremity. The shank segment includes markers on midshank, medial malleolus, and lateral malleolus. The foot segment will be created using a set of markers on the head of the fifth metatarsus, head of the first metatarsus, and posterior surface of the calcaneus. Further, markers will be placed on the right and left acromion process, sternoclavicular notch, and C7 vertebra to create the thorax segment. To create the head segment, 1 marker will be placed on each side of the head.

3D co-ordinates of each reflective marker will be tracked using Qualisys Track Manager. Visual 3D software will be used to process the data files. After placement of markers, a static image of the participant standing in an anatomical position will be taken.

#### AMTI Force Plates

Postural control as the COP movement will be measured with an AMTI force platform (Advanced Mechanical Technology Inc.). The force platform measures the 3 force components, *F_x_*, *F_y_*, and *F_z_* (where *x*, *y*, and *z* are the medial–lateral, anterior–posterior, and vertical directions, respectively), at the sampling frequency of 1200 Hz. The AMTI force plate is a static-force measurement system and is a computer-based system which synchronizes with a computer using a serial link. The COP movement track data (in millimeter) will be collected for each participant and will be converted into mediolateral and anterior–posterior components for analysis.

Participants will stand on the force plate with arms relaxed at their sides. Participants will be asked to stand with their feet shoulder width apart. They will be instructed to maintain their gaze on the letter while maintaining a quiet stance for the duration of a task.

### Experimental Tasks

The experimental tasks have been designed to simulate eye movements in visually complex environments. Tasks will increase in the level of complexity, starting from easy visual tasks progressing to more visually complex tasks. Letters will be projected in a random sequence on to a range of visually complex background images (Figure 4). The font of the letters, backgrounds, and duration of each task were finalized after piloting. There are 6 tasks, each lasting 70 seconds. The letters appear on the screen for 7 seconds each, at different positions on the screen. Python programming language has been used to select letters and their positions on screen. Participants will be instructed to focus on a letter as they appear on the screen. The tasks increase in difficulty in two ways: (1) the background behind the letter progresses from neutral to busy (ie, to a complex moving background), and (2) by the appearance of either a single letter or multiple letters on screen. In the single-letter tasks (tasks 1, 2, 5, and 6), the participants will be instructed to focus their gaze on each projected letter for the duration of the task. In the multiple letters’ tasks (tasks 3 and 4), the participant will be instructed to find letter *E* and maintain visual fixation on it for the duration of the task. The tasks will be presented from the lowest to highest difficulty of background and number of letters (as described in Figure 4). The tasks will not be randomized as the more difficult tasks might provoke symptoms of dizziness which would hinder the performance of participants in the subsequent tasks.

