## Discussion

This is an exploratory study with the primary aim to identify whether fixational instability is associated with motion sensitivity and whether it leads to increased postural sway and altered kinematics in adults with motion sensitivity.

This study will provide a detailed investigation of visual fixations, postural sway, and kinematics in complex visual environments. The use of a mobile eye tracker device will investigate naturalistic eye behavior when exposed to experimental stimuli. The task hierarchy will help in understanding how characteristics of visual fixations change when a person views a complex visual environment as opposed to neutral environments. The experimental tasks might provoke symptoms in some participants; however, we expect that all participants will be able to complete the protocol with appropriate rest intervals between tasks. Our sample size of 20 participants in each group is a foundational step in exploring whether visual fixations contribute to motion sensitivity after vestibular disorder. We anticipate the outcomes will be able to detect a difference between healthy adults and those with motion sensitivity. Results from this study will inform future trials and will be used to inform development of diagnostic and rehabilitation programs.

We hope that this study will increase our understanding of the complex interactions of vision and balance in people with motion sensitivity. If we determine that gaze and postural control characteristics are altered, we will develop an intervention that is designed to re-align the gaze and postural control characteristics closer to those of the control population. This intervention would then be tested in a series of clinical trials to determine effectiveness.

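### Task number is not a single complexity scale, and the fixed order does not let a wider group gap in the later tasks be attributed to complexity alone

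*Protocol article*

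**What the plan says.** The protocol article, Experimental Tasks, describes six tasks of 70 seconds each. It presents them as a ladder: "Tasks will increase in the level of complexity, starting from easy visual tasks progressing to more visually complex tasks". Difficulty is said to rise in two ways: the background moves from neutral to busy and moving, and the display changes "by the appearance of either a single letter or multiple letters on screen". On the sequence it says "The tasks will be presented from the lowest to highest difficulty of background and number of letters", with a reference to Figure 4.

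The allocation of tasks follows in the same section: "In the single-letter tasks (tasks 1, 2, 5, and 6") the participant looks at each projected letter. In tasks 3 and 4 the instruction differs: "the participant will be instructed to find letter *E* and maintain visual fixation on it for the duration of the task".

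The order is fixed for a stated reason: "The tasks will not be randomized as the more difficult tasks might provoke symptoms of dizziness which would hinder the performance" in later tasks. Data Collection provides rest after every task, and Safety Measures adds monitoring and rest; neither fixes a rest length.

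The Hypothesis ties group differences in refixations, centre of pressure and centre of mass to complex visual environments. The Discussion relies on the sequence for this: "The task hierarchy will help in understanding how characteristics of visual fixations change when a person views a complex visual environment" rather than a neutral one.

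**The concern.** The hypothesis is about how the two groups differ as the visual environment becomes more complex. A reader who follows the results from task 1 to task 6 will take a widening gap as the effect of complexity. At least three other things change along that path.

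- **Letter condition.** It does not rise with task number.
- **Nature of the task.** Tasks 3-4 ask for a search as well as a fixation. Under Outcome Measures, a refixation is counted when gaze crosses the 100-pixel dispersion threshold, and a saccade is whatever lies between fixations without meeting the fixation criteria. Search movements meet these definitions, and the article states no exclusion for them. Refixations are the first outcome named in the hypothesis.
- **Position in the session.** The later tasks come after more exposure. The protocol's own reason for not randomising is that provoked dizziness may impair later performance.

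The Discussion plans to develop an intervention if gaze and postural control prove altered. Taking search or accumulated symptoms for an effect of complexity would misdirect that work.

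**Working it through.** The article gives no figure for this point and calls the sample size of 20 per group arbitrary, so there is nothing to reproduce. Three checks were made.

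**1. Does the number of letters rise with task number?** Inputs are from Experimental Tasks; single is coded 0 and multiple 1.

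| Task | 1 | 2 | 3 | 4 | 5 | 6 |
|---|---|---|---|---|---|---|
| Letters | 0 | 0 | 1 | 1 | 0 | 0 |
| Position minus mean (3.5) | -2.5 | -1.5 | -0.5 | 0.5 | 1.5 | 2.5 |

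The sum of products is (-0.5)(1) + (0.5)(1) = 0, so the correlation of letter condition with task order is 0. The sequence falls from task 4 to task 5. This needs only the text, not Figure 4.

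**2. How closely can background follow position?** The backgrounds are in Figure 4, so their coding is an assumption.

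- If background rises at every task, it equals position and r = 1. The two effects cannot be separated at all.
- If it rises in pairs (1, 1, 2, 2, 3, 3), the deviations are -1, -1, 0, 0, 1, 1. The sum of products with position is 2.5 + 1.5 + 1.5 + 2.5 = 8. The sums of squares are 4 and 17.5, so r = 8/√(4 × 17.5) = 8/√70 = 0.96.

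Under either coding there is little or no information with which to separate background from order.

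**3. What could differential carry-over do?** Let the group gap at task k be δ + c(k - 1). Here δ is a constant group difference and c is an extra drift per task, in SD units, in the motion-sensitivity group only. There is no complexity effect.

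- Mean gap in tasks 1-2: δ + 0.5c.
- Mean gap in tasks 5-6: δ + 4.5c.
- Difference: 4c.

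With c = 0.05 this is 4 × 0.05 = 0.2 SD; with c = 0.10 it is 4 × 0.10 = 0.4 SD. With c = 0, which includes any drift shared equally by both groups, it is 0. The drift values are assumptions, as are linearity and the absence of recovery during rest. If rest shrinks c, the result shrinks in proportion.

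**The case against.** The strongest reply is that the plan never tests what is criticised. The Analysis section names one-way between-group analyses of variance with Šidák-adjusted post-hoc comparisons. It names neither a trend over task number nor a late-minus-early contrast. This stands. A reader might infer from check 3 that the planned analysis of variance has an inflated error rate. The document does not support that: the 0.2-0.4 SD belongs to a contrast the article does not specify and rests on a drift that has no source in it.

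Second, the ascending order is reasoned. Carry-over falls on later tasks under any order, and placing the most provocative tasks last protects the easier ones. Rests and monitoring are provided to limit symptoms. This also stands, so the choice of order is not at fault. How much the rests help cannot be known from the document.

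Third, the ordering sentence refers to Figure 4 and might mean a combined ranking, with background first and letters within background. The text can neither confirm nor exclude this. Even so, the number of letters would not rise with task number, and a combined ranking would still not be one scale. It would be going too far to say that the background order is wrong; only the letter part is contradicted by the text.

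Fourth, the study is exploratory and the hypothesis speaks of association. Both groups perform the same search, and time effects they share cancel. That limits the point but does not remove it, because search behaviour and carry-over may themselves differ between groups.

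**Conclusion.** The point holds as a limit on interpretation, together with one sentence to correct. Task number is not a single complexity scale: letter condition runs single, multiple, single, and tasks 3-4 add a search that enters the refixation and saccade counts. Background complexity is also aligned with position in the session, to a degree that depends on Figure 4. Carry-over larger in the motion-sensitivity group would not cancel between groups; the rests reduce it by an unknown amount.

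A reader might infer that all the group comparisons are invalid. They are not: a difference between groups within one task stands as a description of that task at that position. What is not supported is attributing a wider gap in later tasks to complexity alone. The 0.2-0.4 SD shows what a modest assumed drift could produce; it is not an estimate of what happened in this study.

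**What to change.** According to the Results section, data collection is complete and analysis was still to begin, so these are changes to analysis and wording only.

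1. Keep the task order. Correct the ordering sentence so that it no longer says the number of letters rises through the sequence.
2. Code background level and letter condition as two separate factors. Do not analyse or describe task number as a ladder.
3. Estimate the group-by-background contrast within the single-letter tasks, 5-6 versus 1-2. State beside it that this removes the letter and search confound but leaves order and carry-over in place.
4. Analyse tasks 3-4 separately. If refixations are counted only after gaze first reaches the E, report them per second of remaining time. Otherwise a group that finds the E later has a shorter counting window and a lower raw count at the same underlying rate.
5. Word the conclusion as a group difference in this fixed sequence and say that complexity and order are not separated.

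An analysis by letter position within a task (70/7 = 10 periods) should not be offered as a test of carry-over. It does not reach across the rests between tasks, and it mixes time with exposure to that background.

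The cost is fewer tasks per contrast, some extra mapping of gaze to the target in tasks 3-4, and a more cautious conclusion.

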**Figure 4 figure4:**
[figure not shown]
The experimental tasks.
*Letters have been magnified for clear visibility.

### Data Collection

Data will be collected for all tasks in 1 session. The motion analysis system and force plate will be calibrated before the participant arrives in the laboratory. Upon arrival, the participant will be orientated to the laboratory setup. The Dizziness Handicap Inventory and Visual Vertigo Analogue Scale screening will be completed. After setting up the markers, experimental tasks will be explained, and the eye tracker glasses will be fitted for comfort and calibrated. The participant will then stand on the force plate wearing the calibrated eye tracker with reflective markers (Figure 5). During the experimental tasks, appropriate rest intervals will be provided after each task to minimize provocation of symptoms such as dizziness and nausea.

**Figure 5 figure5:**
[figure not shown]
Data collection procedure.

### Outcome Measures

The following outcome measures will be explored and analyzed for this study.

#### Visual Fixations

Fixation characteristics for each group will be computed using the SMI ETG software and will measure the total number of refixations, the maximum fixation duration, and the number of saccades. The software determines a fixation as a window with a minimum duration of 80 ms and a maximum dispersion of 100 pixels. Refixations are calculated if the eye crosses the maximum dispersion threshold of 100 pixels. The fixation duration will be calculated as the total time spent in fixating during a trial. The maximum fixation duration will be calculated as the longest fixation within each trial. A saccade event is computed as any event that does not meet the fixation criteria between the new and the previous fixation.

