#### Sensor Motoric Instruments Eye Tracking Glasses (SMI ETG)

The SMI Eye Tracking Glasses (SMI ETG) are a mobile eye-tracking device with a binocular sampling rate of 120 Hz (Figure 3). SMI uses infrared light of wavelength around 789-880 nm to increase the contrast between the pupil and iris which is easily detected by the camera. SMI is a video-based eye tracker based on the concept of pupil center corneal reflection. The scene camera has a resolution of 1280 × 960 pixels @ 24FPS, 960 × 720 pixels @ 30 FPS with a 60° horizontal and 46° vertical field of view. The gaze position accuracy is 0.5° for all distances and the gaze tracking range is 80° horizontal and 60° vertical.

The SMI software uses a frame-by-frame analysis of the gaze data. These data involve defining the location and type of gaze behavior for each frame of data collected. Frame numbers are used to determine the duration of the eye movement. SMI uses an in-built detector for identifying saccades, fixations, and blinks. According to the detector, a blink is identified by points where eye data are not present, a saccade represents a quick change in gaze location, and a fixation is bordered by 2 saccades.

Data collected by the eye-tracking glasses identify the primary event as fixation and therefore a dispersion-based algorithm is used. The algorithm identifies fixations as groups of successive points within a dispersion, or maximum separation. A blink is determined based on the whole trial data where the pupil diameter is either zero, or the horizontal and vertical gaze positions are zero, or they lie outside a calculated valid pupil range. Once fixations and blinks are identified, a saccadic event is created between the detected blinks and fixations.

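### The fixation outcomes take no account of whether gaze is on the letter, so they cannot separate fixational instability from not doing the task

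*Protocol article*

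**What the plan says.** The instruction is tied to a target. Under AMTI Force Plates the protocol article says of participants: "They will be instructed to maintain their gaze on the letter while maintaining a quiet stance for the duration of a task". Experimental Tasks sets six tasks of 70 s and adds: "The letters appear on the screen for 7 seconds each, at different positions on the screen". In tasks 1, 2, 5 and 6 the target is each single letter in turn. In tasks 3 and 4 it is the letter E among several.

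The outcome definitions are not tied to a target. Visual Fixations gives them as follows:

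- Fixation: "The software determines a fixation as a window with a minimum duration of 80 ms and a maximum dispersion of 100 pixels".
- Refixation: "Refixations are calculated if the eye crosses the maximum dispersion threshold of 100 pixels".
- Fixation duration: "The fixation duration will be calculated as the total time spent in fixating during a trial".
- Maximum fixation duration: "The maximum fixation duration will be calculated as the longest fixation within each trial".
- Saccade: "A saccade event is computed as any event that does not meet the fixation criteria between the new and the previous fixation".

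The eye-tracker section describes the same logic: "The algorithm identifies fixations as groups of successive points within a dispersion, or maximum separation". It also says that the software assigns a gaze location to every frame, but no outcome definition uses that location.

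**The concern.** The Introduction describes fixational instability as frequent saccades and refixations in someone who is trying to fixate. Hypothesis 1 predicts more refixations in people with motion sensitivity. Both readings presuppose that the participant is looking at the letter, or trying to. The definitions do not require this, and nothing in Experimental Tasks, Data Collection or Safety Measures describes a check on it.

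Two things follow. Gaze shifts that the task itself demands are counted in the same way as shifts caused by instability. Time spent looking elsewhere is scored as if it were task performance. If adherence differs between groups or between backgrounds, a difference in refixations or maximum fixation duration could reflect adherence, instability or both. The same values feed the receiver operating characteristic thresholds planned in the Analysis section.

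**Working it through.** The plan gives no figure to reproduce here, and its sample size of 20 per group is stated to be arbitrary. The check uses the task timings.

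**Inputs.** Task length 70 s and letter display 7 s (Experimental Tasks). Minimum fixation 80 ms and dispersion limit 100 pixels (Visual Fixations). Scene camera 1280 × 960 or 960 × 720 pixels over 60° × 46° (eye-tracker section). Screen 135 in., 16:9, at 3.5 m (Experimental Setup). Assumed, because the article does not give them: 0.2 to 0.5 s to reach a new letter, evenly spaced blinks, and successive letters more than 100 pixels apart.

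**1. An adherent participant, single-letter task.**
- Letters per task = 70 / 7 = 10.
- Gaze shifts needed = 10 − 1 = 9, each crossing the dispersion threshold and so counted as a refixation.
- Longest on-letter fixation = 7 s at most, or 7 − 0.5 = 6.5 s to 7 − 0.2 = 6.8 s after allowing for the shift.

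**2. Is the letter-spacing assumption reasonable?** If the 100 pixels are scene-camera pixels (the article does not say), the limit is between 100 × 60 / 1280 = 4.7° and 100 × 46 / 720 = 6.4°. The screen is 2.99 m wide and 1.68 m high, and so spans about 46° × 27°. Letters placed at varied positions could often be further apart than the limit, but the task figure is not available to confirm it.

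**3. A participant who holds gaze on one spot off the letter, taking a trial as the 70-s task.**
- Refixations = 0, against at least 9 for the adherent participant.
- Longest fixation with *b* blinks = 70 / (*b* + 1).

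| Blinks in 70 s | Longest fixation |
|---|---|
| 0 | 70 s |
| 2 | 23.3 s |
| 4 | 14 s |
| 9 | 7 s |

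At 9 evenly spaced blinks the advantage on maximum duration has gone. The advantage on refixations remains, because a refixation is defined by crossing the dispersion limit and not by a blink.

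**4. The same participant, taking a trial as one 7-s letter window.** The article does not define *trial*. On this reading the off-letter participant has 0 refixations against at least 1 in each window that begins with a shift, and a longest fixation of up to 7 s against 6.5 to 6.8 s. The ordering is the same, but the gap in duration is small.

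**5. A participant who leaves the letter and scans.** Each excursion beyond 100 pixels adds a refixation. This participant scores as unstable.

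Steps 3 and 5 describe two forms of the same failure to follow the instruction, and the outcome moves in opposite directions. In tasks 3 and 4 the search for E adds further instructed gaze shifts. Whether E moves every 7 s cannot be confirmed, so the 7-s ceiling is claimed only for tasks 1, 2, 5 and 6.

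**The case against.** The strongest reply is that a journal article condenses the protocol, and that gaze mapping and trial-validity rules are usual contents of a longer document. The frame-by-frame gaze location shows that the means exist. It is true that the article nowhere says adherence will go unchecked, and a fuller document may contain an on-target rule. But the article does not leave these outcomes open. It writes out the rule for each one, and followed as written those rules ignore location.

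A reader might go further and infer that the bias runs against hypothesis 1, because people with motion sensitivity avoid busy places and so would look away from the moving background. The documents do not support that. The Introduction speaks of avoiding environments such as supermarkets, not of averting gaze during a short supervised task. It also says that fixating a target suppresses the optokinetic response to background motion. On that account, leaving the letter while still viewing a moving background could raise saccades and refixations, which is towards the hypothesis.

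A reader might also try to size the effect. If 5 of 20 cases stared elsewhere for 20 s without a blink, their group's mean maximum duration would rise by at least 5/20 × (20 − 7) = 3.25 s. Every behavioural input there is invented, the result needs a trial to be the 70-s task, and it concerns maximum duration, whereas hypothesis 1 names refixations. It does not show that the main result would be cancelled or reversed.

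Finally, restricting the refixation count to on-letter gaze would not be enough. A participant who never looks at the letter would still score zero, and excursions from the letter, which are the instability of interest, would be discarded. That objection stands, and the fix below is built to meet it.

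**Conclusion.** The definitions are badly fixed for the construct. As written, they count about 9 instructed gaze shifts per single-letter task as refixations, and they score steady gaze off the letter as stable fixation. An off-letter participant can have 9 or more fewer refixations per task than an adherent one. Any advantage on maximum duration ranges from tenfold (70 s against 7 s, no blinks) to none (9 evenly spaced blinks), and is slight if a trial is one letter window. Scanning away from the letter raises the counts instead.

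The 9 shifts rest on letter spacing above 100 pixels. How many participants would leave the letter, in which group, and in which manner is not given, so neither the direction nor the size of a group bias can be stated. What can be said is that a group difference in these outcomes, or its absence, could not be attributed to fixational stability alone. This deserves correction before analysis, although the study is exploratory.

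**What to change.** Using the recorded gaze location, the scene video and the stimulus letter positions, define an area of interest around the current letter (E in tasks 3 and 4), and state what a trial is. Then:

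- In each letter window, exclude the initial shift to a new letter and start counting once gaze has reached it.
- Count later departures from the letter and returns to it as refixations, so that excursions are kept.
- Take maximum fixation duration from on-letter fixations only.
- Treat a window in which the letter is never reached as off-task, not as zero refixations. Give counts per scored window, so that lost windows do not lower them.
- Report percentage time on letter by group and task.
- Keep the location-free counts as a sensitivity analysis.

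The Results section says that data collection had finished and analysis had not begun, so this could be settled in advance. It needs no new participants or procedures. The cost is analyst time for gaze mapping.
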